### 2.9. Procedure

Potential participants will be initially screened according to the inclusion and exclusion criteria by our recruitment team, and those who may meet the eligibility requirements will be subjected to RA related serological testing for secondary evaluation. Eligible participants who are willing to take part in this trial will be asked to sign a written informed consent form after completing the screening tests. Then, all of eligible patients will be randomized to group A, group B, or group C. After randomization, subjects enter a 1-week baseline period then they will complete the baseline questionnaire and blood sampling at 4 equidistant time points within 24 hours. Subsequently, they will receive a 6-week moxibustion in the light of their group allocation and then provide blood specimens at 4 equidistant time points within 24 hours. After 3 weeks and 3 months, blood sample will be also collected. All the RA subjects will be evaluated with study-related scales before treatment, as well as 3 weeks, 6 weeks and 3 months after treatment. Three months after the end of treatment, all participants will be followed up to assess the curative effect and safety (Table 1).

**Table 1 T1:** The schedules for patient enrollment, interventions and assessments. SF-MPQ, short-form Mcgill pain questionnaire; DAS28, disease activity score of 28 joints.

Study schedule					
	Baseline	Treatment phase (Weeks 1–6)			Follow-up phase
Timepoint	Week –1	Week 0	Week 3	Week 6	Month 3
Patients					
Enrollment	√				
Informed consent	√				
Signed informed consent		√			
Medical history	√				
Physical examination	√				
Laboratory test	√				
Randomization		√			
Intervention					
Moxibustion at 7–9 am		√	√	√	
moxibustion at 5–7 pm		√	√	√	
Waiting list group					
Outcomes					
SF-MPQ	√		√	√	√
Laboratory indicators	√		√	√	√
Joints morning Stiffness score	√		√	√	√
Joints swelling index	√		√	√	√
Joints tenderness index	√		√	√	√
DAS28	√		√	√	√
Monitor					
Adverse events					√
Patient’s compliance					√
Reasons of drop-outs or withdrawals					√

DAS28 = disease activity score 28, SF-MPQ = Short-Form McGill Pain Questionnaire.

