#### 2.11.1. Primary outcome.

##### 2.11.1.1. Short-Form McGill Pain Questionnaire (SF-MPQ).

The SF-MPQ is a multidimensional measure of perceived pain in adults with chronic pain, including pain due to rheumatic diseases. It includes 3 items: the Pain Rating Index, Present Pain Intensity, and Visual Analog Scale (VAS) for average pain. The Pain Rating Index is comprised of 15 words (11 sensory and 4 affective), and each selected word is scored from 0 (none) to 3 (severe). The total Pain Rating Index score is obtained by summing the item scores (range 0–45). Scores on the Present Pain Intensity range from 0 to 5 and on the VAS from 0 to 10. A higher score on the SF-MPQ indicates worse pain.

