### 2.17. Ethics

This study protocol will be carried out in accordance with the Declaration of Helsinki, and it was approved by the Medical Ethics Committee Board of the Affiliated TCM Hospital of Southwest Medical University, Luzhou, Sichuan, China (number: KY2021065-FS01). Once recruited, each participants would be requested to voluntarily sign a written informed consent form as acceptance in this research study before randomization. The present study is financially supported by the funds for the special project of scientific research on TCM Bureau of Sichuan Province (No. 2021MS084) and the National Natural Science Foundation of China (NO. 81804208). This study protocol has been registered at Chinese Clinical Trials Registry with the identifier number: ChiCTR2100051532.

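### Screening blood tests precede the written consent signature, and section 2.9 and Table 1 disagree on whether baseline assessment comes before or after it

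*Protocol article*

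**What the plan says.** Section 2.9 (Procedure) describes two screening steps. The recruitment team first checks people against the criteria, and "those who may meet the eligibility requirements will be subjected to RA related serological testing for secondary evaluation". Those found eligible and willing then "will be asked to sign a written informed consent form after completing the screening tests". Randomization follows, and after it the baseline: "After randomization, subjects enter a 1-week baseline period then they will complete the baseline questionnaire and blood sampling".

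Table 1, in the same section, has two consent rows. One, labelled only as informed consent, is ticked at Week -1. The other, "Signed informed consent", is ticked at Week 0, in the same column as randomization and the first moxibustion. Also ticked at Week -1 are enrollment, medical history, physical examination, the laboratory test, SF-MPQ, laboratory indicators, morning stiffness, the swelling and tenderness indices, and DAS28. SF-MPQ is the primary outcome (2.11.1).

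Section 2.4 has the practitioner verify eligibility and the signed form before opening the envelope. Section 2.17 states conduct under the Declaration of Helsinki and asks participants, once recruited, to "voluntarily sign a written informed consent form as acceptance in this research study before randomization".

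**The concern.** A blood test ordered by a recruitment team to decide trial entry is a trial procedure. The article fixes the order as blood first and signature second, and its only stated safeguard is the step before randomization. A site that follows section 2.9 as written will take trial blood from people who have not agreed in writing, including some who will fail screening or decline. This is hard to square with the ethical standard that 2.17 invokes.

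The second part concerns the baseline. Four hospitals work from this schedule. One that follows Table 1 collects the primary baseline before the signature and before randomization. One that follows the text of 2.9 collects it after both. Patients are not blinded (2.5) and SF-MPQ is self-reported, so under the text the baseline pain score is given after the patient may already know the group.

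**Working it through.** The article gives no figure to reproduce. The check is to set out the order of events in each place.

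| Step | Text of 2.9 | Table 1 |
|---|---|---|
| Initial check against criteria | First | Not shown separately |
| Unspecified informed-consent row | Not mentioned | Week -1 |
| Screening laboratory test | After the initial check | Week -1 |
| Signed consent | After the screening tests | Week 0 |
| Randomization | After signed consent | Week 0 |
| Baseline SF-MPQ and laboratory indicators | After randomization, following a one-week period | Week -1 |
| First treatment | After baseline | Week 0 |

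1. *Screening blood against signature.* In the text, serology comes before the signature, stated outright. In Table 1 the laboratory test is one column before the signature. This reads the Week -1 laboratory test row, which is grouped with history and examination, as the screening serology. The text of 2.9 does not depend on that reading.

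2. *Does another section repair this?* Section 2.4 requires the signature before the envelope is opened. Section 2.17 requires it before randomization. Section 2.6 lists a signed form as an inclusion criterion without a time. All three are satisfied by a form signed after the blood test, so none corrects the order.

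3. *Baseline against signature.* In Table 1 the baseline outcomes precede the signature (Week -1, then Week 0). In the text they follow it. The orders are opposite.

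4. *Baseline against randomization.* In the text a one-week baseline period separates randomization from the baseline measurements. In Table 1 randomization and first treatment share Week 0 and the baseline is the week before. These also cannot both hold.

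5. *Who is affected by item 1.* Only people who pass the initial check go to serology. Every randomized RA patient has passed both steps, so if recruitment reaches its target the number is at least 90. To this are added those who fail serology or then decline, for whom the article gives no number.

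**The case against.** **The article is condensed, and an ethics committee approved the study.** The full protocol and consent form are not shown and may be in better order. But this is not a gap left by condensing: the article states an order in the text, its table is compatible with that order, and approval does not reconcile the two on baseline timing.

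**The Week -1 consent row may already cover screening.** It could mean information given, verbal agreement or consent to screening. The article does not say, and this uncertainty stands. The row cannot be taken as the signature, which has its own row one column later, and it does not alter the sequence in the text.

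**The serology may be routine care.** For some outpatients and inpatients it may be. Section 2.3 also recruits by posters and online advertising, but gives no proportions, so one cannot say that most or many of those tested come from outside care. The point rests on the stated purpose of the test, which is eligibility.

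**Stronger readings that do not hold.** A reader might infer that the whole primary baseline, and 90 × 4 = 360 timed blood samples, are taken before any signature. That joins Table 1's timing to a sampling scheme that Table 1 does not show. Section 2.9 places the four-sample day after consent and randomization, and 2.11.2.1 says only that it is before treatment. A reader might also infer that everyone screened gives blood before signing, but those who fail the initial check do not reach serology.

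**The trial's comparisons are untouched by late consent.** This is largely right. People who decline before randomization never enter the compared groups, and nothing in the article shows bias in the estimates from the consent order. The consent issue is ethical and procedural.

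**Conclusion.** The concern holds in two parts of unequal strength.

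The first is firm: eligibility serology comes before the written signature in 2.9, Table 1 is compatible with that, and 2.4 and 2.17 protect only the step before randomization. It applies to RA patients who pass the initial screen, at least 90 at full recruitment. It assumes that the serology is done for the trial, as 2.9 describes it.

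The second is a contradiction and not an established breach. Table 1 places the baseline outcomes, including SF-MPQ, before the signature; 2.9 places the baseline after consent and randomization. The article does not show which one sites will follow, so it cannot be concluded that the primary baseline is collected without signed consent. The two statements must be reconciled and the Week -1 consent row defined or removed.

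The article needs correcting because a stated rule bears on participants' rights at first contact. The correction changes neither the sample size nor the analysis.

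**What to change.** - **Section 2.9:** limit the initial screen to existing records and interview. Obtain signed consent next, then do the serology and any other trial tests, then confirm eligibility.
- **Table 1:** replace the two consent rows with one signed-consent row at Week -1, placed ahead of the laboratory test and all outcome rows.
- **Section 2.17:** require the signature before any trial-specific procedure, not only before randomization.
- **Sections 2.4, 2.9 and Table 1:** state one sequence: signed consent, screening tests, baseline assessment, randomization, treatment. The sentence in 2.9 that puts the baseline after randomization must change with the rest; moving the signature alone would leave the baseline contradiction in place. In 2.4, the practitioner would check that the signed form and the completed baseline are on file before opening the envelope.

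The cost is small: edits to the text and one table, notification of the ethics committee, and staff time to consent some people who then fail screening.

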### 2.5. Blinding

Taking into account that the significant difference of treatment and the specificity of moxibustion, patients will understand their group allocation, so will the operators, meaning that double blinding the study is unfeasible. Consequently, we will strictly carry out random allocation in order to ensure the integrity of this research, meanwhile, the efficacy assessors and outcome statisticians should be blinded to avoid the bias resulting from subjective impression.

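### Section 2.9 takes the baseline after an open randomisation while Table 1 takes it before; the two orders must be reconciled so that the self-reported baselines precede the envelope.

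*Protocol article*

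**What the plan says.** The text of section 2.9 (Procedure) runs in this order. Patients are screened, including serology, and "will be asked to sign a written informed consent form after completing the screening tests". Next: "Then, all of eligible patients will be randomized to group A, group B, or group C". Only then come the baseline measures: "After randomization, subjects enter a 1-week baseline period then they will complete the baseline questionnaire and blood sampling at 4 equidistant time points". Treatment follows.

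Table 1, captioned "The schedules for patient enrollment, interventions and assessments", gives another order. All six outcome rows (SF-MPQ, laboratory indicators, morning stiffness, swelling, tenderness, DAS28) are ticked at Week -1 and none at Week 0. Randomisation is ticked only at Week 0, the column in which moxibustion starts. The row "Signed informed consent" is also ticked only at Week 0, although a separate informed-consent row is ticked at Week -1.

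On blinding, section 2.5 says "patients will understand their group allocation, so will the operators, meaning that double blinding the study is unfeasible", and that "the efficacy assessors and outcome statisticians should be blinded to avoid the bias resulting from subjective impression". Section 2.4 has the practitioner open the envelope once eligibility and signed consent are confirmed. Section 2.11.1 makes the SF-MPQ, a scale of perceived pain, the primary outcome.

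**The concern.** A baseline should be fixed before anyone knows the allocation, so that it cannot depend on it. Under the section 2.9 text, a patient could already know that he or she is on the waiting list, or is to receive moxibustion, when completing the baseline pain questionnaire. Blinded assessors do not protect a patient's own report. If the two kinds of patient answer differently, that difference enters every analysis that subtracts or adjusts for baseline.

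The text order also puts a week between randomisation and the start of treatment. Someone who leaves in that week has been randomised but may have no baseline, and would meet the section 2.8 withdrawal criterion for patients who received no trial treatment. Under the Table 1 order, someone who leaves in the baseline week has not yet been randomised.

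With four hospitals working from one protocol, two stated orders also mean that sites may differ in when they take the baseline.

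**Working it through.** The document gives no figure to reproduce on this point. The check compares the stated orders and then sizes the possible effect under assumptions.

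**Comparing the orders**

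1. Section 2.9 text: screening tests, signed consent, randomisation, 1-week baseline period, baseline questionnaire and four-point bloods, treatment.
2. Table 1: baseline outcomes at Week -1; signed consent, randomisation and first treatment at Week 0. There is no column for a baseline week between randomisation and treatment.
3. Sections 2.11 and 2.11.2.1 place these measures only before treatment, which fits either order and does not settle it.
4. Two details are less certain. Table 1 does not name the four-point blood series, so its place at Week -1 is inferred from the laboratory row. The text could mean that the baseline measures fall at the end of the week rather than during it; in either case they follow randomisation.
5. Consent: sections 2.4 and 2.17 require signature before randomisation, and Table 1 is compatible with that. But Table 1 puts the signature after the Week -1 laboratory test and all baseline outcomes, and the text puts it after the screening tests.

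**Illustrative size**

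Assumptions, none of which is a figure for this bias in the document: 26 patients analysed per group (the minimum in section 2.12), equal SDs, no true effect, two-sided 5% test, normal approximation, baseline-to-outcome correlation ρ of 0.3 to 0.7, and a shift b of 0.1 to 0.3 SD in one arm's baseline caused by knowing the group.

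- Change from baseline: bias = b; SE = √(4(1−ρ)/n).
- Baseline as covariate: bias = ρ·b; SE = √(2(1−ρ²)/n).
- Post-treatment values only: bias through the baseline = 0.
- False-positive rate = 1 − Φ(1.96 − bias/SE) + Φ(−1.96 − bias/SE).

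Example with b = 0.2 and ρ = 0.5:

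- Change score: SE = √(4 × 0.5/26) = 0.277; bias/SE = 0.72; rate 11.1%.
- Covariate: bias = 0.5 × 0.2 = 0.10; SE = √(2 × 0.75/26) = 0.240; bias/SE = 0.42; rate 7.0%.

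| Shift b (SD) | Change score: bias (SD) | Change score: false-positive rate | Covariate: bias (SD) | Covariate: false-positive rate |
|---|---|---|---|---|
| 0.1 | 0.1 | 6.1% to 7.5% | 0.03 to 0.07 | 5.1% to 6.4% |
| 0.2 | 0.2 | 9.4% to 15.4% | 0.06 to 0.14 | 5.6% to 10.9% |
| 0.3 | 0.3 | 15.0% to 28.7% | 0.09 to 0.21 | 6.3% to 18.5% |

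The ranges run over ρ from 0.3 to 0.7. The table shows that a modest shift could matter. It does not show that one will occur.

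**The case against.** The best reply is that Table 1 already has the sound order, so this is an inconsistency and not a settled decision to take the baseline after randomisation. That is right, and the point is put as a conflict to be reconciled. It still matters, because the text is explicit and a site could follow it.

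The remaining objections limit the reach of the point:

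- **Size.** A reader might express an assumed baseline shift as a share of the planning effect. From section 2.12 that effect is (4.86 − 4.17)/√((0.94² + 1.40²)/2) = 0.69/1.19 = 0.58 SD. But it is a DAS28 effect, and the primary outcome is SF-MPQ, for which no planning effect is given. The ratio would mix two outcomes and rest on an assumed shift.
- **Analysis.** A reader might infer that every treatment comparison is biased. Section 2.13 plans one-way ANOVA and names neither change scores nor baseline adjustment for the treatment effect, so the lower bound is zero.
- **Blood results.** A reader might extend the concern to the serum markers. Nothing in the document suggests that knowing the group alters them.
- **Contrast and direction.** Groups A and B both expect moxibustion, so the comparison of treatment times is largely unaffected. For the waiting-list contrasts the direction is unknown: if group C over-reported pain at baseline, its change score would look better, against moxibustion.
- **Disclosure.** Section 2.5 says that patients will know their group but not when. That they know it by the baseline visit is inferred from sections 2.4 and 2.5, though nothing in the plan withholds it.
- **Missing baselines.** Section 2.13 plans intention-to-treat analysis with multiple imputation. This keeps such patients in the analysis, but an imputed baseline is weaker than one measured before randomisation.
- **Consent.** This is a separate matter from bias and adds nothing to its size. It belongs here because the same table has to be corrected.

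**Conclusion.** The point holds as a contradiction between the text of section 2.9 and Table 1, with a plausible but unquantified risk if the text is followed. The risk concerns the self-reported baselines (SF-MPQ, morning stiffness, the patient-reported part of DAS28), mainly in comparisons of moxibustion with the waiting list, and it includes randomised patients lost before their baseline. It rests on two conditions: that patients know their group when the baseline is taken, and that baseline enters the analysis as a change score or covariate. If only post-treatment values are compared, no bias arises through the baseline.

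The document does not support a stated percentage bias, a claim that the blood results are biased, or a claim that the morning-versus-evening comparison is compromised. The order still needs to be settled before enrolment, because a baseline taken after allocation cannot be retaken.

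**What to change.** 1. Rewrite section 2.9 to the Table 1 order: complete all baseline scales, joint assessments and the four-point 24-hour sampling in the baseline week, and only then open the envelope. Have group participation, whether treatment or waiting, begin directly after randomisation.
2. Name the four-point series in the laboratory row of Table 1, so that its place before randomisation is explicit.
3. Reconcile the consent rows: move the signature from Week 0 to before the study-specific Week -1 assessments, and make the section 2.9 text agree.
4. If any patient has already been enrolled under the text order, state which order was used.

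The cost is a reordering of steps in the text and small edits to Table 1, with no extra visits, tests or patients.

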### 2.10. Interventions

Moxibustion staff members who have more than one year experience in Du moxibustion will be called for this trial and retrained for standard operation before the trial. The moxibustion acupoints are identified in accordance with the method of acupoint location issued by the World Health Organization (WHO).^[15]^ Du moxibustion treatment will be carried out from DU14 (Dazhui) to DU1 (Changqiang). The patient will be in prone position with bare back and be covered with a strip of gauze to prevent scalding. Large and long moxibustion box (60 cm long) will be placed on the back to cover the acupoints. Place the moxa velvet evenly in the moxibustion box (about 3 cm in height and 2 cm in width), ignite the moxa velvet from the top, and let it burn from top to bottom. Remove the ash of moxa after it is burned out (Fig. 2). The total time of moxibustion each time is about 30 minutes. After the treatment, the moxibustion box will be removed, with the degree of local skin flush and no blister. Moxibustion treatment will be conducted 3 times a week for 6 weeks. The patients will be followed up for 3 months. Patients in group A and B will be treated with Du moxibustion at 7 to 9 am and 5 to 7 pm, respectively. The group C will not receive any adjunctive treatment during the trial period, and then accept moxibustion treatment after the investigation. During the trial, the patients in each group will maintain the routine drug treatment.

**Figure 2. F2:**
[figure not shown]
Du moxibustion.

### 2.11. Outcomes

All of the outcomes will be assessed for 4 times before the treatment, as well as 3 weeks, 6 weeks, and 3 months after treatment (Table 1).

#### 2.11.1. Primary outcome.

##### 2.11.1.1. Short-Form McGill Pain Questionnaire (SF-MPQ).

The SF-MPQ is a multidimensional measure of perceived pain in adults with chronic pain, including pain due to rheumatic diseases. It includes 3 items: the Pain Rating Index, Present Pain Intensity, and Visual Analog Scale (VAS) for average pain. The Pain Rating Index is comprised of 15 words (11 sensory and 4 affective), and each selected word is scored from 0 (none) to 3 (severe). The total Pain Rating Index score is obtained by summing the item scores (range 0–45). Scores on the Present Pain Intensity range from 0 to 5 and on the VAS from 0 to 10. A higher score on the SF-MPQ indicates worse pain.

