### 2.4. Randomization and allocation concealment

Eligible patients will be randomly assigned to 3 groups in a 1:1:1 ratio. The computer-generated random number list will be concealed in sequentially numbered, opaque, and sealed envelopes which kept by an independent custodian to ensure allocation concealment. The patients’ screening sequence numbers will be printed on the outside while the group names will be printed inside the envelope. The practitioner will firstly verify each patient meet the eligibility criteria and sign the written informed consent form, and then open the sealed envelope which containing an allocation sequence number for each patient. If any error or disclosure regarding randomization occurs, a new randomization sequence will be generated starting from the problematic serial number and applied to subsequent patients from then on.

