### 2.13. Statistical analysis

To eliminate artificial error, two statisticians blinded to the whole trail process will independently perform the statistical analysis by using SPSS statistics software (version 21) and Halberg cosiner software.

Baseline data including age, sex, disease duration, SF-MPQ score, joints morning stiffness score, joints swelling index, joints tenderness index, DAS28 score and laboratory indicators results before interventions will be analyzed with different approaches. All the data will be presented as mean ± standard deviation (SD). If the continuous variables can meet a normal distribution and homoscedasticity, One way analysis of variance (ANOVA) with multiple comparisons will be applied to identify differences more than two groups, while Student *t* test for pairwise comparison. Otherwise, we will use Tamhane T2 method instead. Halberg cosiner software will be used to analysis the circadian rhythm. *P* value is under .05 will be taken as statistically significant for each outcome. We will select the intention-to-treat principle to perform this statistical analysis. Thus, missing data will be imputed by using the multiple imputation method.

We will use two different methods: intention-to treat and per-protocol, for sensitivity analysis.

Halberg cosiner software will be utilized to analysis the circadian rhythm. For using the program, we will create time series per file (with the time tag, mean and SD). Then, the program will fit the cosine curve and polar coordinates and judge whether the parameters can show a circadian rhythm. By the formula of cosine curve, the results will be given, such as mesor, amplitude, acrophase. The results were considered significant when the *P* value <.05.

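### The primary outcome fixes no SF-MPQ score, visit or group contrast, so P<.05 for each outcome does not hold a 5% error rate for a primary claim

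*Protocol article*

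**What the plan says.** **Scores.** Section 2.11.1.1 of the protocol article names the SF-MPQ as primary and says of it: "It includes 3 items: the Pain Rating Index, Present Pain Intensity, and Visual Analog Scale (VAS) for average pain". The ranges are 0–45, 0–5 and 0–10. Items are summed only within the Pain Rating Index. The section adds "A higher score on the SF-MPQ indicates worse pain", but gives no rule for forming one score from the three parts.

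**Visits.** Section 2.11: "All of the outcomes will be assessed for 4 times before the treatment, as well as 3 weeks, 6 weeks, and 3 months after treatment". That is one baseline and three later assessments, none marked as primary.

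**Groups.** Section 2.4: "Eligible patients will be randomly assigned to 3 groups in a 1:1:1 ratio". Three groups give three pairs. Section 2.1 asks two questions, whether moxibustion works and which time of day is better, but no comparison is named as primary.

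**Tests.** Section 2.13 plans a one-way ANOVA with multiple comparisons of an unspecified kind, and Student's t "test for pairwise comparison. Otherwise, we will use Tamhane T2 method instead". A P "value is under .05 will be taken as statistically significant for each outcome".

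**The concern.** A primary outcome lets one pre-specified result carry the trial's claim at a stated error rate. Here three things are open together: which part of the SF-MPQ is read, when it is read, and between which groups. The only stated error rate, .05, is set outcome by outcome. Nothing in the section limits the error over the scores and visits that could each be reported as the primary result.

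The sample size in section 2.12 does not settle the choice, because it rests on DAS28, which section 2.11.2 lists as secondary.

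The visit wording adds to the uncertainty. Table 1 places Week 3 and Week 6 inside the treatment phase (Weeks 1–6), while the Abstract and sections 2.9 and 2.11 place the 3-week and 6-week assessments after treatment. If no primary reading is fixed, a nominally significant SF-MPQ result cannot be interpreted at the 5% level for either of the trial's questions.

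**Working it through.** **The plan's own figure.** The article states no overall error rate for the primary outcome, so there is none to reproduce. Its only figure is .05 for each outcome.

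**Inputs from the article**
- Scores: 3 (section 2.11.1.1)
- Post-baseline visits: 3 (section 2.11 and Table 1)
- Groups: 3, hence 3 pairs (section 2.4)
- Patients per group: 30 (section 2.12)
- Threshold: .05 (section 2.13)

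**Assumptions, not in the article**
- Tests are two-sided.
- Data are multivariate normal.
- The correlation between scores equals that between visits, and is varied from 0 to 0.9.

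**Step 1: independent tests.** The chance of at least one P<.05 among m independent tests is 1 − 0.95^m.
- One score, three visits, one ANOVA each: 1 − 0.95³ = 14.3%
- Three scores by three visits, one ANOVA each: 1 − 0.95⁹ = 37.0%
- The same with three pairs each: 1 − 0.95²⁷ = 75.0%. This is too high even with uncorrelated scores and visits, because the three pairs share groups.

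**Step 2: simulation under no effect.** There were 10,000 trials per row for the first three result columns and 20,000 for the last two. Entries are the percentage of trials with at least one nominally significant primary result.

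| Correlation | 3 scores × 3 visits, t tests ungated and unadjusted | 3 × 3, t tests only after a significant ANOVA | 3 × 3, pairs Bonferroni-adjusted at each score and visit | One score, 3 visits, ungated t tests | One score, 3 visits, ANOVA |
|---|---|---|---|---|---|
| 0 | 69 | 37.5 | 33 | 32 | 14 |
| 0.5 | 58 | 30 | 27 | 28 | 12 |
| 0.7 | 47 | 24 | 22 | 25 | 11 |
| 0.8 | 40 | 19 | 17 | 22 | 10 |
| 0.9 | 30 | 15 | 13 | 19 | 8 |

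**Step 3: one score at one visit.** Three unadjusted t tests give about 12%. The ANOVA alone, or t tests read only after it, gives 5%. So naming the score and visit removes most of the excess, and handling the three pairs removes the rest.

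**Step 4: the visit wording, side by side**
- Table 1: Week 3 and Week 6 fall within the treatment phase; Month 3 is follow-up.
- Abstract, section 2.9 and section 2.11: 3 weeks, 6 weeks and 3 months after treatment.
- Section 2.11.2.1: four-point blood sampling 6 weeks after the treatment, and further tests after a 3-week and a 3-month intervention, although section 2.10 gives a 6-week course.
- Section 2.9, closing sentence: "Three months after the end of treatment, all participants will be followed up to assess the curative effect and safety". This fixes the origin of the 3-month visit but not of the other two.

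Taken literally, a visit 6 weeks after treatment falls six weeks later than Table 1's Week 6.

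**The case against.** A reader might infer that all 27 score-visit-pair tests are run unadjusted, that any one below .05 counts as success, and so that the false-positive chance is about 40–60%. The article does not support this. It states no such success rule. It plans an ANOVA with multiple comparisons, and Tamhane T2, the fallback, is itself adjusted across pairs. The 40–60% figure also needs correlations of about 0.5 to 0.8, which the article does not give. At those correlations, using the ANOVA as a gate brings the figure to about 19–30%.

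The article can also be read as meaning one SF-MPQ score: section 2.13 speaks of that score in the singular. On that reading the ANOVA figure is only 8–14%. The reading is fair, but no such total is defined.

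The visit wording may be mostly loose English, since Table 1 and the closing sentence of section 2.9 together suggest a workable schedule. That is plausible, but the passages still disagree as written.

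Finally, this is a condensed article and the analysis plan is not shown, so the choice of multiplicity procedure could properly sit there. That stands for the procedure. It does not cover a primary outcome that the article itself describes as three scores without a total, a .05 rule that it does state, or visits that it describes in conflicting ways.

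**Conclusion.** The point holds in conditional form. The primary outcome is not fixed to one score, visit or contrast, and the stated .05 rule does not control the error across them. With 30 per group and assumed correlations from 0 to 0.9, the chance of at least one nominally significant primary result under no effect is:
- about 15–38% if the ANOVA gates the pairwise tests;
- about 30–70% if the t tests are ungated and unadjusted;
- about 8–14% if one SF-MPQ score was meant and ANOVA is used at each of the three visits.

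No single percentage can be attached to the plan, because the article does not say which of these applies. Every reading examined that leaves the visit open exceeds 5%. The figures rest on normal data, two-sided tests and equal correlations between scores and between visits.

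**What to change.** 1. Name one primary score, for example the total Pain Rating Index, at one visit, for example Week 6 at the end of the treatment course.
2. Name the comparisons that answer section 2.1: moxibustion versus waiting list, and group A versus group B. Test them with a familywise procedure such as Holm at an overall two-sided 0.05.
3. Decide whether A and B are pooled against C or each compared with C; this is the sponsor's choice. Pooling lowers the variance factor from 1/30 + 1/30 = 0.067 to 1/60 + 1/30 = 0.050, a quarter less. But if only one time of day works, the pooled contrast estimates half that effect.
4. Label the remaining scores, visits and pairs as secondary.
5. Reconcile the after-treatment wording in the Abstract and sections 2.9, 2.11 and 2.11.2.1 with the Week 3, Week 6 and Month 3 columns of Table 1, stating the origin from which each visit is counted.

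**Cost.** With two comparisons, Holm tests the smaller P value at 0.05/2 = 0.025 and, if that succeeds, the larger at 0.05. With three comparisons the first step is 0.05/3 = 0.017. No extra data are needed. The study is registered and ethics-approved, so the change needs an amendment and a registry update, made before anyone sees outcome data by group.
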